### 2.2. Eligibility Criteria

To be included in the program, participants must (i) have a left ventricle ejection fraction higher than 30% after stroke and (ii) be aged between 18 and 80 years. As exclusion criteria, the following will be taken into account: (i) the presence of absolute or relative contraindications for accomplishing the treadmill test, as indicated by the Spanish Society of Cardiology; (ii) ongoing treatment for other diseases or regularly taking a drug(s) that has/have a direct or indirect effect on the nervous system (e.g., anxiolytics, antidepressants, or neuroleptics); (iii) the absence of medication to control or modify cardiovascular disease during the intervention; (iv) people who are participating or have participated in other similar exercise programs in the previous three months; and (v) inability to perform at least 80% of the workouts during the intervention.

The cardiologist from University Hospital Torrecárdenas will verify that the patients meet the inclusion criteria. The trial steering members will certify that the subjects do not meet any of the exclusion criteria. The study requirements will be explained to patients in detail verbally and via the written patient information and consent form. The model consent form is shown in Appendix A.

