Therefore, HRV is a biomarker that can indicate the health status of the cardiovascular system, serving as an effective tool for individualizing the training load in cardiac patients. Moreover, it can be used to measure cardiovascular responses to therapeutic interventions, with HIIT-based exercise being the most recommended option. However, with the goal of obtaining improved results regarding cardiovascular rehabilitation, it is still unclear whether to opt for HIIT training or to individualize HIIT training using HRV. We hypothesize that (i) both HIIT training and HRV-guided training will improve cardiorespiratory fitness, functional performance, heart rate variability, relative weight and fat distribution, inflammatory markers, cognitive function, and quality of life in post-stroke patients but that HRV-guided training will achieve better results; and (ii) HRV-guided training will be safer and more feasible and will generate more patient adherence to the program. The primary objective of the proposed protocol is to determine the effect of HIIT- compared to HRV-guided training on cardiorespiratory fitness in post-stroke patients who undertake an 8-week cardiac rehabilitation program. The secondary aims of this trial are (i) to determine the effect of HIIT training compared to HRV-guided training on heart rate variability scores in post-stroke patients, (ii) to investigate the effect of each exercise program in terms of the adaptations obtained in functional parameters, body composition, and the quality of life of these patients, (iii) to study the effect of both programs on inflammatory markers, (iv) to determine which exercise program is more effective at improving cognitive function, and (v) to analyze whether the two exercise programs are equally feasible and safe, as well as to evaluate their effect on patient adherence to the cardiac rehabilitation program.

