The training prescribed to the HRV-G group will depend on the subjects’ daily HRV and will follow the HRV-training schema designed by Kiviniemi et al. (2007) [36] (Figure 1). The HRV registration procedure and analysis are described by Carrasco-Poyatos et al. (2020) [37], although, in accordance with the results from recent randomized controlled trials [38,39] and the characteristics of the sample, only high or low intensity will be considered for the present protocol.

The assigned study intervention will be modified or discontinued if the drug dose changes in response to harms, the participant requests it, the disease worsens, or the cardiologist recommends it. Compliance with the exercise protocol will be controlled by the nurse.

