#### 2.4.1. VO_2peak_

In accordance with the Spanish Cardiology Society, a modified version of the Bruce protocol will be used as the treadmill test, as it is indicated for elderly people and those considered high risk. Unlike the Bruce protocol, in the modified version, stage 1 starts at a 0% gradient, walking at 45.5 m/min. During stages 2 and 3 (at 3′ and 6′), the percentage gradient increases by 5% each time. Therefore, 6′ more exercise is performed at low intensity. From there, the percentage gradient will increase by 2% every 3′, and the walking speeds will be 67 m/min, 91 m/min, 112.5 m/min, and 136.8 m/min in Stages 4–7, respectively [40]. Pulmonary gas exchange will be measured from the beginning of the rest period until the end of the test using a metabolic system (Parvo TrueOne 2400, ParvoMedics Inc., East Sandy, UT, USA or MetaMax3B, Cortex Biophysik, GmbH, Leipzig, Germany). Prior to the test, participants will be asked to avoid exercise, caffeine, and tobacco for 24 h and food for 2 h but to take all the usual medications. In accordance with Taylor et al. (2017) [41], VO_2_peak will be determined from the average of the two highest values attained in 10 s periods, disregarding outliers when the difference between the two highest VO2 values is greater than 200 mL/min divided by the participant’s body weight. Additionally, an electrocardiogram recording will be taken during the rest period and during the test. Endothelial parameters, such as systolic and diastolic blood pressure and heart rate, will be recorded during the rest period and during the 1 min and 5 min post tests. Work parameters, such as the protocol stages performed, the maximum velocity and gradient reached, the test duration, and the reason for ending it will also be recorded.

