#### 2.4.2. Heart Rate Variability

Taking into account the sample characteristics, we propose that the HRV be measured over a 60 s period with the subject lying down at rest just prior to the training session. This procedure, modified from Plews et al. (2017) [42], will allow the multidisciplinary team to manage data recording, maintaining the same conditions and position, thus obtaining more reliable data [43]. The HRV4Training smartphone application will be used. This tool was validated by Plews et al. (2017) [42] and employed in several studies, as it facilitates data measurements, providing either temporal (rMSSD, pNN50, and SDNN) or frequential (LF and HF) measurements using photoplethysmography. Data can be downloaded directly to a computer in the form of an Excel sheet.

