## Figures and Tables

**Figure 1 ijerph-19-10868-f001:**
[figure not shown]
HRV-guided training schema [36]. When LnrMSSD7-d is within the normal range, high-intensity training sessions will be prescribed. If LnrMSSD7-d falls below the normal range, low intensity or rest will be prescribed. Low = exercise at 65% of maximal heart rate, High = exercise at 85% more of maximal heart rate, Rest = resting day, HRV+ = increased or unchanged HRV; HRV− = decreased HRV.

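### Section 2.2 sets no heart-rhythm requirement, although beat-interval HRV steers HRV-G training and is secondary aim (i); for any patient not in stable sinus rhythm the HRV value does not measure autonomic function

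*Protocol article*

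**What the plan says.** **Eligibility (section 2.2).** Participants must "i) have a left ventricle ejection fraction higher than 30% after stroke and (ii) be aged between 18 and 80 years". The five exclusions concern treadmill-test contraindications, other treatment or drugs acting on the nervous system, absence of cardiovascular medication, recent similar exercise programmes, and inability to do 80% of the workouts. The one closest to heart rhythm is "the presence of absolute or relative contraindications for accomplishing the treadmill test, as indicated by the Spanish Society of Cardiology". Sinus rhythm, atrial fibrillation, pacing and ectopy are not mentioned.

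**Role of HRV.** Section 2.3: "The training prescribed to the HRV-G group will depend on the subjects’ daily HRV". Figure 1 gives the rule: "When LnrMSSD7-d is within the normal range, high-intensity training sessions will be prescribed", and "If LnrMSSD7-d falls below the normal range, low intensity or rest will be prescribed". The first secondary aim in the Introduction is "i) to determine the effect of HIIT training compared to HRV-guided training on heart rate variability scores in post-stroke patients".

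**Measurement (section 2.4.2).** HRV is a 60 s supine reading before the training session, taken with a smartphone application "providing either temporal (rMSSD, pNN50, and SDNN) or frequential (LF and HF) measurements using photoplethysmography". Section 2.3 refers the registration procedure and analysis to a cited paper.

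**ECG (section 2.4.1).** At the treadmill test, "Additionally, an electrocardiogram recording will be taken during the rest period and during the test". Section 2.4 places that test one week before and one week after the intervention. The text does not link the ECG to eligibility or to the validity of the HRV reading.

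**The concern.** The Introduction justifies HRV as an index of the balance between parasympathetic and sympathetic activity. That reading of beat-interval variation presupposes beats that start in the sinus node. In atrial fibrillation the variation comes from the arrhythmia, in a paced rhythm the device sets the intervals, and an ectopic beat with its pause adds large interval differences unrelated to vagal tone.

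The population is post-stroke, aged up to 80 and in cardiac rehabilitation, so such rhythms are foreseeable. The Introduction itself lists ventricular arrhythmia among conditions that go with low HRV, whereas uncorrected ectopy would make the reading high.

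Two things are at stake. For an affected patient in either arm, the HRV outcome is not a measurement of what secondary aim (i) asks about. For an affected patient in HRV-G, the sessions follow a number that carries no autonomic information, so the patient does not receive the intervention under test.

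**Working it through.** The documents give no figure on rhythm, so there is none to reproduce. The check asks how far a non-sinus rhythm moves the reading, in which direction, and for how many patients.

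**Formula.** rMSSD = √(mean of squared successive interval differences).

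**1. One uncorrected premature beat, single reading.** Assumptions: mean interval 900 ms, 66 intervals in about 60 s (65 differences), true rMSSD 20 ms, one beat 300 ms early followed by a pause 300 ms longer.
- Background sum of squares: 65 × 20² = 26,000.
- Added differences −300, +600, −300: 90,000 + 360,000 + 90,000 = 540,000.
- rMSSD = √(566,000 / 65) ≈ 93 ms. LnrMSSD goes from 3.00 to 4.54.

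With 70 beats per minute, true rMSSD 15 to 30 ms and a beat 20 to 30% early, one such beat gives about 53 to 82 ms.

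**2. The same beat after averaging.** The rule uses LnrMSSD7-d. There are three sessions a week (section 2.3) and the reading precedes the session (section 2.4.2). If only those readings enter the seven-day value (assumption), one contaminated reading in three shifts it by (4.54 − 3.00) / 3 ≈ 0.51 log units. That is a factor of e^0.51 ≈ 1.7, from 20 to about 33 ms.

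**3. Sustained atrial fibrillation.** Taking intervals as independent, rMSSD = √2 × SD. With SD 150 ms this is about 212 ms. With a mean interval of 857 ms and a coefficient of variation of 0.10 to 0.25, it is about 121 to 303 ms.

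**4. What the rule does with it.**
- *Intermittent arrhythmia or ectopy:* the affected reading is too high. When the reference readings are clean, it moves the patient away from the below-range branch of Figure 1.
- *Permanent atrial fibrillation, range taken from the patient's own readings (assumption):* the range shifts with the reading. In a simulation of single 60 s readings (independent intervals, coefficient of variation 0.20), 16% fell below the patient's own mean − 1 SD and 30% below mean − 0.5 SD by chance. The decision is then mostly noise.

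**5. How many.** The share is not in the documents. At an assumed 5%, 0.05 × 30 = 1.5; at 25%, 0.25 × 30 = 7.5. That is about 2 to 8 of 30 per arm (section 2.5).

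**6. Effect on the contrast.** If guidance has no specific effect in affected HRV-G patients (assumption), an effect δ of guidance shrinks to (1 − share) × δ: 0.95δ at 5% and 0.75δ at 25%.

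**The case against.** **Some of these patients may never enrol.** The treadmill exclusion removes relative as well as absolute contraindications, and the exclusion for other treatment or nervous-system drugs may catch some treated arrhythmia. This stands as a limit on the number: the outside list is not shown, so the documents do not establish that a patient with controlled atrial fibrillation is eligible. But an exclusion about exercise-test safety is not a requirement that HRV be interpretable.

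**The cited HRV procedure may correct ectopic beats.** It may, and the 93 ms figure applies only to an uncorrected beat. Beat filtering would not turn sustained atrial fibrillation into an autonomic measurement.

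**A reader might infer that the rule always errs towards the more intense session and so undermines the safety hypothesis.** The documents do not support that. In permanent atrial fibrillation against an own range, the signal is mostly noise. Ectopy in the reference readings would raise the range and make later clean readings look low. Seven-day averaging also shrinks the effect of a single beat.

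**A reader might infer that the trial's comparison as a whole is invalid.** That is not supported either. VO2peak comes from gas exchange. Randomisation is expected to place affected patients in both arms, and section 2.8 adjusts for baseline and moves to rank tests for non-normal data. These limit how far a few extreme values can move the HRV comparison. They do not make those values measure autonomic function, and they do not restore HRV guidance to the patients who lack it.

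**Conclusion.** The point holds for a subset of patients and should be corrected. Section 2.2 as written can admit patients whose HRV is not an autonomic measurement, while HRV is both the treatment-decision variable in one arm and the first secondary aim. For each such patient the HRV outcome is invalid, and in HRV-G the treatment contrast is diluted. The error in a reading is upward with intermittent arrhythmia or uncorrected ectopy, and the training signal is mostly noise in permanent atrial fibrillation judged against the patient's own range.

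The size rests on assumptions: the interval values in steps 1 to 3, three readings per seven-day value, and a share of 5 to 25%, or about 2 to 8 of 30 per arm. The true share may be smaller if the unseen contraindication list or HRV procedure removes or corrects cases. Measurement of VO2peak is unaffected; only the contrast in treatment received could touch the primary comparison.

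**What to change.** 1. Add to section 2.2 a requirement of stable sinus rhythm, checked on the resting ECG already recorded at the pre-intervention treadmill test.
2. State that HRV readings taken outside sinus rhythm after randomisation are invalid for the HRV outcome, and how such a reading is recognised. One ECG a week before the start will miss intermittent arrhythmia, so the first change does not make this one unnecessary.
3. State that the patient stays in the intention-to-treat analysis of VO2peak. Say also how the invalid HRV values are handled, because the last-observation rule in section 2.8 would otherwise replace them with an older reading.

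How a patient without a usable HRV signal then trains is for the investigators to decide.

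A rule for unusable recordings alone would be lighter. It would protect the HRV outcome, but would leave patients with a permanent non-sinus rhythm in HRV-G without any guiding signal.

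Cost: an amendment to the eligibility and HRV text, with no new procedure for the entry check. The recruitment pool shrinks by the excluded share (5 to 25% on the assumption above), and the results apply only to post-stroke patients in sinus rhythm.

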### 2.3. Interventions

To implement this protocol, it will be necessary to include a physical exercise graduate in the multidisciplinary group (described in Section 2.1), who will design and conduct the intervention. This will ensure that patients are controlled, monitored, and directed by a specialist at all times, thus guaranteeing the safety of the protocol and optimizing the intervention.

The intervention program will be conducted over a period of 8 weeks, with three one-hour sessions/week. Every session will comprise a warmup, the main intervention, and a cooldown. The warmup and cooldown will last 10–12 min, respectively, and will be based on the dynamic mobilization of the main muscle groups, especially those of the lower body, to prepare and recover them, respectively, for the main part of the intervention. In the main part, lasting 30–35 min, aerobic-based exercise will be implemented. To reduce mechanical limitations while carrying out the exercise, both a treadmill and a cycloergometer will be used, rotating them weekly, as recommended by a recent meta-analysis [34]. Motivational strategies, such as playing music during the session and giving messages of encouragement, will be used by the professionals supervising the activity. The periodization of the intervention will include two training periods: a two-week familiarization period (FP) and a 6-week training period (TP). The FP will be common to both groups and will be used to increase the training intensity gradually to prepare the patients for the high-intensity TP. In the TP, each group will carry out the corresponding intervention. The HIIT-G group will train according to a predefined high-intensity training program. Taking into account that VO_2_ can be improved either with short or long HIIT intervals [9] and that patients are expected to be in poor physical condition, short training intervals of 1′30′′ will be combined with active rest periods. In each session, the work time at the determined intensity will be at least 50% of the total work interval. The training interval intensity will be gradually increased as the rest periods are reduced. In accordance with Taylor et al. (2017) [35], both the maximal heart rate and the subjective perception of effort will be controlled. The HIIT-G training periodization is presented in more detail in Table 1.

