#### 2.4.8. Exercise Adherence, Feasibility, and Safety

Adherence will be assessed by the number of sessions completed by the participants. At least 80% of sessions should be completed to consider adherence successful. Feasibility will be considered compliance with the exercise protocol and will be recorded as the percentage of participants that finish every training session. Safety will be measured as the number of adverse events occurring during the training sessions. In accordance with Villelabeitia-Jaureguizar et al. (2017) [54], these will be recorded as mild, moderate, or severe. Moreover, their relation to the exercise session will also be taken into account. All these variables will be recorded by the multidisciplinary group present at the exercise sessions.

The time schedule for enrolment, interventions, and assessments is shown in Figure 2.

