### 2.8. Data Analysis

The data monitoring committee will have full access to the complete final dataset. The data will be analyzed using Jamovi (Jamovi Project 2018, version 0.9.1.7, Jamovi, Sydney, Australia) and RStudio 3.15.0 software. Prior to data analysis, the Kolmogorov–Smirnov test and the Levene test will be performed to determine the normal distribution of the variables and the homogeneity of variance. For a variable to be considered as having a normal distribution, 95% of values will have to be within two standard deviations of the mean. Descriptive data will be reported as mean ± SD and range. All data will be analyzed based on the intention-to-treat principle (the last observation carried forward). If the sample is normally distributed, the Student’s *t*-test for independent samples will be used to compare the two intervention groups for the pretest, whereas ANCOVA will be used for the post-test, using the basal scores and age as covariables. Moreover, the Student’s *t*-test for related samples will be calculated to compare variables before and after the intervention in each group. If the sample is non-parametric, Kruskal–Wallis and the Mann–Whitney U tests will be used, respectively. The standardized mean differences (Cohen’s effect size) will be calculated together with the 95% confidence intervals [56]. The effect sizes (ESs) will be calculated using Cohen’s d (Hopkins). The relationship between variables will be assessed using the Pearson r correlation coefficient. If r is higher than 0.7, the determination coefficient (r^2^) will be used to determine the percentage of Y variation with regard to the X variation. Significance will be accepted at *p* ≤ 0.05.

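### Exclusion criterion (v) is most naturally read as depending on attendance after randomisation; applied that way, it contradicts intention to treat and empties the 80% adherence outcome

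*Protocol article*

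**What the plan says.** Section 2.2 gives five exclusion criteria. The fifth is "inability to perform at least 80% of the workouts during the intervention". The same section assigns the check without saying when it is made: "The trial steering members will certify that the subjects do not meet any of the exclusion criteria".

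Section 2.8 sets the analysis principle: "All data will be analyzed based on the intention-to-treat principle", with the last observation carried forward.

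Section 2.4.8 makes the number of completed sessions an outcome and sets a threshold for it: "At least 80% of sessions should be completed to consider adherence successful". Hypothesis (ii), at the end of the Introduction, predicts that HRV guidance will be safer, more feasible and better adhered to than HIIT.

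On the content of HRV-G training, section 2.3 says that "only high or low intensity will be considered for the present protocol". The Figure 1 legend says: "If LnrMSSD7-d falls below the normal range, low intensity or rest will be prescribed".

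**The concern.** An eligibility criterion should be decidable before allocation. Whether a patient gets through 80% of the workouts is settled during the eight weeks that follow, and the assigned programme can influence it. Section 2.3 allows the intervention to be modified or stopped at the patient's request, when the disease worsens or on the cardiologist's advice. A patient who stops early enough for one of these reasons falls below 80%.

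If such patients were excluded, three things would follow:

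- VO2peak, the primary outcome, would be compared between selected completers rather than between the groups as randomised.
- The selection would probably differ by arm, because the trial itself expects adherence to differ.
- The adherence comparison would be made only among patients who had already passed the adherence threshold.

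**Working it through.** **1. The cut-off in sessions.** Section 2.3 states: "The intervention program will be conducted over a period of 8 weeks, with three one-hour sessions/week". That is 8 × 3 = 24 sessions, and Table 1 runs from S1 to S24. Then 0.80 × 24 = 19.2, so at least 20 sessions are needed: 20/24 = 83.3% passes and 19/24 = 79.2% fails. Five uncompleted sessions put a patient below the line, for criterion (v) and for adherence success alike.

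**2. Sections 2.2 and 2.8 side by side.** Take a randomised patient with 19 of 24 sessions. Under section 2.8 the patient is analysed in the assigned arm. Under criterion (v), read as attendance during the programme, the patient is excluded. The article does not say which governs, so the primary analysis population is not fixed.

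**3. Sections 2.2 and 2.4.8 side by side.** If everyone below 20 sessions is excluded, the proportion successful among those retained is 100% in each arm, whatever the true adherence. The session count is not fixed, but it can only run from 20 to 24 (83.3% to 100%).

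**4. Size of the selection effect on VO2peak (illustration).** The SD of 4.75 mL/kg/min is from section 2.5. The exclusion rates and the correlation r between attendance and VO2peak are assumptions; the documents give neither. Suppose attendance tendency and VO2peak are jointly normal and the lowest fraction p of attenders is removed. The retained mean then rises by SD × r × φ(z_p)/(1 − p), where φ is the standard normal density and z_p the p-quantile. The factor φ(z_p)/(1 − p) is 0.195 at p = 10%, 0.350 at 20% and 0.497 at 30%. The spurious difference, in favour of the arm that loses more patients, is:

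| r | 10% v 20% excluded | 10% v 30% excluded |
|---|---|---|
| 0.2 | 0.15 | 0.29 |
| 0.3 | 0.22 | 0.43 |
| 0.5 | 0.37 | 0.72 |

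For example, 4.75 × 0.3 × (0.497 − 0.195) = 0.43 mL/kg/min. Under this model, equal exclusion rates with equal r give no difference. These figures are for unadjusted means; the planned adjustment for baseline would change them. For scale, section 2.5 works with an error of 1.7 mL/kg/min.

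**5. Loss of power.** The stated 97% is reproduced with 30 per group only at a standardised difference of 1 (two-sided 0.05): Φ(√(30/2) − 1.96) = 97.2%. On the same basis, excluding 10%, 20% or 30% from each group leaves 27, 24 or 21, with power 95.7%, 93.4% or 90.0%. Lost numbers are therefore the smaller problem; selection is the larger one.

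**6. Rest days (conditional).** The arms differ in the six-week training period, 6 × 3 = 18 sessions. If the Figure 1 legend governs, and if a prescribed rest day counts as a workout not performed, five rest days (5/18 = 27.8% of that period) leave a fully compliant HRV-G patient with at most 19/24. With an assumed rest probability per session and independent sessions, the chance of five or more rest days in 18 is:

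| Rest probability | Chance of five or more | Expected among 30 |
|---|---|---|
| 10% | 2.8% | 0.8 |
| 15% | 12.1% | 3.6 |
| 20% | 28.4% | 8.5 |
| 25% | 48.1% | 14.4 |
| 30% | 66.7% | 20.0 |

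If section 2.3 governs, there are no rest days and this route disappears.

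**The case against.** The strongest reply is that removal after randomisation is never stated. Criterion (v) stands among screening items, speaks of inability rather than failure to attend, and is certified by steering members. Criterion (iii) also refers to the period of the intervention, so such wording can describe a state expected at entry. The intention-to-treat rule with last observation carried forward, and a success threshold that some patients must be able to miss, both suggest that low attenders are kept. This stands as far as it goes: the screening reading is possible, and the contradiction is conditional. It does not rescue the wording. Section 2.2 gives no baseline test of the expected inability, and the same words would license dropping a randomised patient.

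A reader might also infer that adherence is 100% by construction and that hypothesis (ii) cannot be tested at all. The documents do not support that. Only the success proportion among retained patients would be fixed. The session count would be truncated but could still differ between arms, and safety and feasibility are separate measures, although they too would be affected by selection.

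Finally, a reader might infer that HRV-G patients will be excluded for obeying prescribed rest. That needs the Figure 1 legend to override section 2.3, rest to be chosen over low intensity, and an unstated rule that a rest day is a missed session. What stands is an inconsistency and an undefined count.

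**Conclusion.** The point holds in conditional form. Criterion (v) is most naturally read as resting on behaviour after randomisation. So applied, it conflicts with section 2.8, selects patients at rates the trial expects to differ by arm, fixes adherence success at 100% in both groups among those retained, and confines the session count to 20–24. Under the assumed correlations and exclusion rates, the spurious VO2peak difference runs from about 0.15 to 0.7 mL/kg/min. The documents supply neither input, so this shows scale and is not a forecast. The cut-off of 20 of 24 sessions follows directly from the protocol. It should be corrected because the primary analysis population depends on it. The rest-day issue is a separate inconsistency whose effect depends on how it is resolved.

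**What to change.** - **Section 2.2:** delete criterion (v), or restate it as a judgement on expected ability to attend, made and recorded before randomisation.
- **Section 2.8:** state that every randomised patient is analysed in the assigned arm whatever the attendance. Use the 80% rule only to define a secondary per-protocol set.
- **Section 2.4.8:** keep 80% as the adherence-success threshold, with all randomised patients in the denominator.
- **Section 2.3 and Figure 1 legend:** reconcile the two statements on rest. If rest days remain, state how a prescribed rest day counts in the adherence measure. One option is to divide sessions completed by sessions prescribed, under the same rule in both arms.

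The cost is wording only. Low attenders remain in the primary analysis, which may dilute the estimated effect slightly; the intention-to-treat principle already chosen accepts this.
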